## Data management

All data are registered using an electronic Case Report Form (eCRF). Monitoring is performed according to Good Clinical Practice (GCP) guidelines. The eCRF provides data on age, demographics, background medical data, and initial tumour and lymph node characteristics deriving from clinical, radiological and histopathological assessment, details concerning type, dose and duration of neoadjuvant and adjuvant systemic therapy, as well as histopathological results at surgery and data on follow-up. Data are managed by the Clinical Trial Office at Centre for Clinical Cancer Studies, Karolinska University Hospital, Stockholm, Sweden. Security is comparable to bank security with encrypted data.

Recorded information is pseudonymised and the key kept at each responsible site. Keys may however need to be transferred to trial staff for quality assurance purposes such as central review of pathology slides and central review of imaging. Information is confidential and the database is privacy-protected; i.e., no data can be traced back to the patient in research reports and no unauthorized individuals may have access to the data about individuals in the database. The database will be maintained until further notice (at least 20 years after inclusion of the last patient) and be reported in accordance with General Data Protection Regulation (GDPR). The authority responsible for the database is Karolinska Institutet, Stockholm, Sweden.

The Neo-ACT trial is registered at www.clinicaltrials.gov (NCT05184582).

## Monitoring and follow-up

This prospective trial is conducted according to GCP guidelines and monitored by the Clinical Trial Office at Centre for Clinical Cancer Studies, Karolinska University Hospital, Stockholm, Sweden, for Swedish sites, and further CROs in further countries participating in this trial. CROs will be monitoring inclusion and exclusion criteria as well as completeness and accuracy of data recorded in the eCRF by regular on-site visits. To this end, participating units will grant access to patient medical files in due time on request. Patients are informed about monitoring procedures and medical file access in the patient information leaflet and grant their consent to these by signing the consent form.

Each patient is followed up for two years regarding secondary endpoints. Follow-up can be conducted as telephone call or by post, and also includes access to the participant’s medical file in order to check for survival and recurrence. Follow-up must be performed within +/- two months from the surgery date, and data are to be completed in the eCRF within one month from the follow-up date. Long-term follow-up regarding survival and recurrence is conducted via national registers.

Participating sites that do not adhere to GCP guidelines or to the agreements stated in the contract signed between the medical responsible at the individual site and the Clinical Trial Office may be excluded from this trial.

## End of trial

The trial will end for each participant followed for two years after the date of surgery, but also for participants who die, withdraw consent or are lost to follow-up.

## Adverse Events

An Adverse Event (AE) is any untoward medical occurrence in a patient or a clinical investigation subject which does not necessarily have a causal relationship with the trial intervention. An AE can therefore be any unfavourable or unintended finding, symptom, or disease temporally associated with a trial intervention, whether or not related to it.

Patients will be instructed to report the occurrence of AEs in the mobile application. The local investigator will only document AEs of specific interest in relation to the intervention, which are exercise-related AEs

- requiring treatment or talking to a doctor or other health professional
- causing any persistent worsening of participants’ health or well-being, new occurrence of substantial pain or swelling e.g. muscle tear
- occurring during or after the exercise session and requiring restrictions/alterations or early termination of the exercise, or any treatment or clarification by a physician

As some examples, patient-experienced severe pain after exercise is reported as an AE if it requires contact with a treating physician; muscle tears occurring during the exercise session is reported as AE; dizziness or nausea during the exercise session resulting in early termination of the exercise session is reported as an AE. Changes in the exercise program due to recent oncological treatment or due to presence of metastases are *not* reported as AE. The local investigator assesses and records the AEs observed during the AE reporting period: from the date of patient consent signature up to 24 months after randomization. **No AEs related to NACT should be reported.**

A Serious Adverse Event (SAE) (ClinO, Art. 63) is any untoward medical occurrence that results in death or is life-threatening, requires in-patient hospitalisation or prolongation of existing hospitalisation, results in persistent or significant disability or incapacity, or causes a congenital anomaly or birth defect. Local investigators make a causality assessment of the event to the trial intervention (see table below). Any event assessed as possibly, probably or definitely related is classified as related to the trial intervention. **No AEs related to NACT or adjuvant therapy should be documented as an SAE.**

Causality of AEs to trial intervention is assessed according to the following scale:

| Not related | The AE is clearly not related to the trial intervention. It is independent of trial intervention, or evidence prevails that it is related to other aetiology. |
| --- | --- |
| Unlikely | The AE is doubtfully related to the trial intervention. Temporal association between the AE and the trial intervention and the nature of the AE is such that the trial intervention is not likely to have had any reasonable association with the observed AE (cause and effect relationship improbable but not impossible). |
| Possibly | The AE may be related to the trial intervention. Less clear temporal association; other aetiologies also possible. |
| Probably | The AE is likely related to the trial intervention. Clear-cut temporal association; a potential alternative aetiology is not apparent. |
| Definitely | The ae is clearly related to the trial intervention. Clear-cut temporal association, and no other possible cause. |

Severity assessment: Local investigators make a severity assessment of the event according to the Common Terminology Criteria for Adverse Events Version 5 published November 27, 2017^34^.

| Grade 1 | Mild; asymptomatic or mild symptoms; clinical or diagnostic observations only;  intervention not indicated. |
| --- | --- |
| Grade 2 | Moderate; minimal, local or non-invasive intervention indicated; limiting age-appropriate instrumental ADL. |
| Grade 3 | Severe or medically significant but not immediately life-threatening;  hospitalization or prolongation of hospitalization indicated; disabling; limiting  self-care ADL. |
| Grade 4 | Life-threatening consequences; urgent intervention indicated. |
| Grade 5 | Death related to AE. |

A Semi-colon indicates ‘or’ within the description of the grade. ADL: activities of daily living

AEs have to be reported as SAE only when they are related (possibly, probably, definitely) to trial intervention. AEs related to NACT or adjuvant therapy are not considered as a SAE and are therefore exempted from expedited reporting. Trial intervention-related SAEs are documented and reported immediately (within a maximum of 24 hours) to the Principal Investigators.

All AEs will be followed until they have abated, or until a stable situation has been reached. Depending on the event, follow-up may require additional tests or medical procedures as indicated, and/or referral to a general physician or a medical specialist.

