## Population

Clinically T1-3, N0-2 BC patients scheduled for NACT and surgery with curative intent and fulfilling all inclusion criteria and no exclusion criteria as listed below. Patients with oligometastases scheduled for such curative treatment are eligible. Baseline stratification is performed based on treating hospital and biological tumour subtype (ER+HER2-, ER+HER2+, ER-HER2+, ER-HER2-) prior to randomization.

Eligible patients are identified at pre-NACT multidisciplinary team conferences and then receive information about the trial by their oncologist or surgeon, avoiding undue delays. Informed consent is mandatory before randomization and can be obtained by physician or nurse with the appropriate delegation. All participants will undergo standardised tests of physical condition and strength before start of NACT and after NACT but before surgery.

| **Inclusion criteria** | **Exclusion criteria** |
| --- | --- |
| - Patients with primary invasive breast cancer cT1-T3 cN0-2 - Full tumour biology available before initiation of NACT (ER, PR, HER2, tumour grade, and Ki67) - Written informed consent - Age ≥ 18 years | - Bilateral invasive breast cancer - Pregnancy or breast-feeding - The presence of musculoskeletal, neurological, respiratory, metabolic or cardiovascular conditions that may prevent safe completion of the exercise and testing demands of the study - Currently performing equal to or more than 150 mins of moderate to high intensity aerobic exercise and 2 sessions per week of moderate intensity resistance exercise (WHO criteria) |

In case of pre-term abortion of NACT, participants may remain on the trial. Participants who have not received at least four treatment cycles (three weekly treatments of e.g. paclitaxel correspond to one treatment cycle) as NACT are excluded from per-protocol analyses (see statistical analysis plan).

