## Study calendar

| ***Time point*** |  | |
| --- | --- | --- |
| Baseline (before initiation of NACT) | - Verify eligibility - Informed consent - Three 14G tumour biopsies in addition to diagnostic biopsy* - Blood and plasma samples (4-5 x 10 ml) * - Faeces samples * - Full tumour biology (ER, PR, HER2, tumour grade, and Ki67)   Baseline questionnaires and testing   1. EORTC QLQ-C30 (quality of life) 2. EORTC QLQ-B23 (quality of life, breast cancer) 3. Sense of coherence (SOC-13) 4. Godin Leisure Time Self-Reported Physical Activity questionnaire 5. Self-Efficacy of Exercise (SEE) questionnaire 6. Hand grip muscle strength test 7. 1-RM leg press test 8. Ekblom-Bak submaximal cardiorespiratory cycle test 9. Amsterdam Cognition Scan 10. BMI, body fat composition, haemoglobin levels, blood pressure, demographics and medical history | |
| **Randomization** | ***Standard*: Usual care**  ***Intervention*: Physical exercise intervention** | |
| Pre-surgery | Repeat baseline questionnaires and testing (1.-2., 4.-8., 10.)  Device-measured physical activity (Fitbit activity tracker)  Blood (4-5 x 10 ml) and faeces samples *.  Record toxicity-related outcomes and treatment details (CRF) | |
| Surgery | Breast and axillary surgery: endpoint pCR assessed and recorded.  Tumour tissue collected and stored at trial biobank* | |
| Postoperative treatment | Adjuvant treatment as per clinical routine | |
| **Follow-up (years after surgery)** | **1** | **2** |
| EORTC QLQ-C30* | x | x |
| EORTC QLQ-B23* | x | x |
| Record recurrence and survival | x | x |
| Godin (physical activity)* | x | x |
| SEE scale | x |  |
| Amsterdam Cognition Scan | x |  |
| Faeces sample * | x |  |
| Device-measured physical activity (Fitbit activity tracker) | x |  |
| Self-reported sick leave | x | x |

* Stockholm sites only

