## Tumour microenvironment

Baseline presence and composition of tumour-infiltrating lymphocytes (TILs) are prognostic in triple-negative and HER2-positive breast cancers treated with neoadjuvant systemic therapy, and predictive for pCR^48,49^. TILs will be assessed by pathologists in the untreated primary tumour biopsy and the surgical specimen according to international guidelines (<https://www.tilsinbreastcancer.org/>). Even beyond TILs, the tumor microenvironment plays a crucial role in the response to neoadjuvant chemotherapy. Our hypothesis is that the study intervention (physical exercise) can improve pCR rates in tumors that are immunologically cold at baseline.

A study-specific tumor biopsy will be obtained from all study participants before start of neoadjuvant therapy (baseline biopsy) and will be formalin-fixed and paraffin embedded (FFPE). Similarly, tumor material will be obtained from the surgical specimen. Whole sections will be used for H&E staining and subsequently scanning for digital pathology and deep-learning image analyses. Tumor infiltrating lymphocytes (TILs) will be correlated with clinical characteristics and outcomes. Tissue microarrays (TMAs) will be fabricated and will be used for multiplex immunofluorescence assays for characterization of tumor cells, immune and other cell types in the tumor stroma both at baseline and at surgery. For this purpose. the 7-color IHC method (Opal 7 Solid Tumor Immunology Kit, PerkinElmer) using a panel of lymphocytic and macrophage markers and an additional panel of fibroblast, blood vessel and mesenchymal cell markers will be utilized. Multispectral fluorescent scanning (Vectra 3 Quantitative Pathology Systems) and image analysis with compatible software will be used for the visualization and quantitation of the multiple markers in a spatial tissue context.

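### AE recording opens at consent, but harm from study-specific biopsies and research blood sampling has no AE or SAE route, and harm from the strength and cycle tests has no clear one

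*Protocol*

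**What the plan says.** **AE and SAE rules (Protocol, Adverse Events).** The general definition is broad: an AE "does not necessarily have a causal relationship with the trial intervention". The recording period is long and opens before an arm is assigned: "from the date of patient consent signature up to 24 months after randomization". What is written down within it is narrow: "The local investigator will only document AEs of specific interest in relation to the intervention, which are exercise-related AEs". For serious events, "AEs have to be reported as SAE only when they are related (possibly, probably, definitely) to trial intervention". Every level of the causality scale is worded against the trial intervention alone.

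**Procedures outside the exercise programme.**
- The Study calendar lists at baseline, above the randomisation row, "Three 14G tumour biopsies in addition to diagnostic biopsy", as well as research blood samples. Both carry an asterisk, explained below the table as "Stockholm sites only".
- The Tumour microenvironment section has a different scope: "A study-specific tumor biopsy will be obtained from all study participants before start of neoadjuvant therapy".
- The Population section requires physical testing in both arms: "All participants will undergo standardised tests of physical condition and strength before start of NACT and after NACT but before surgery". In the Study calendar these are handgrip, 1-RM leg press and submaximal cycle tests, without an asterisk.

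**Other relevant text.** Patients report AEs through the mobile application (Adverse Events), but only the intervention group is told to download it (The mobile application). Ethical considerations promises recording of cardiovascular and musculoskeletal symptoms during the chemotherapy period, with no restriction by arm, and says that participants with serious adverse events leave the trial. Unplanned hospital admissions during neoadjuvant chemotherapy are a secondary endpoint.

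**The concern.** The recording window and the recording filter do not fit each other. The window opens when trial-specific procedures can begin, but the filter admits only events tied to exercise and the intervention. Relatedness to an exercise programme cannot sensibly be judged for a participant who has not been randomised, or for a control who never receives it.

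The protocol treats testing as a demand of its own: the exclusion criteria name it beside exercise among the things a participant must be able to complete safely. Yet the AE rules have no category for it, nor for biopsies or blood draws.

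Safety oversight is at stake. The data monitoring committee is to review the rate of adverse events and whether the intervention arm fares worse (Handling missing values and deaths). It cannot weigh procedure-related harm that the rules do not call for. Where the text is ambiguous, sites may record the same kind of event differently. The primary analysis of pCR is not affected.

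**Working it through.** The point rests on comparing text. The only arithmetic is the count of test sessions.

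**1. Each procedure against the two rules**

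| Procedure | Who and when | Exercise-related AE? | Related to the trial intervention (SAE)? |
|---|---|---|---|
| Three extra 14G cores | Stockholm, baseline (Study calendar) | No | No |
| Study-specific biopsy | All participants, baseline (Tumour microenvironment) | No | No |
| Research blood sampling | Stockholm, baseline and pre-surgery | No | No |
| Strength and cycle tests, baseline | All, before randomisation | Unclear | Hard to assess; no arm assigned yet |
| Strength and cycle tests, pre-surgery | All, both arms | Unclear | Unclear in the exercise arm; hard to assess in controls |

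For example, a biopsy bleed that leads to admission meets the seriousness definition in Adverse Events but fails the relatedness condition, so it is not reportable as an SAE. It is not exercise-related either, so the documentation rule does not call for it.

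**2. Why the tests are unclear rather than excluded**
- For inclusion: a cycle or leg-strength test is physical exertion. Of the three criteria listed under the documentation rule, only the third mentions the exercise session.
- Against inclusion: the rule ties these events to the intervention, the worked examples concern exercise and exercise sessions, and the exclusion criteria name testing separately from exercise.

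**3. Whether other text closes the gap**
- Ethical considerations is wider than Adverse Events, and the two conflict. It covers only the chemotherapy period, so it misses baseline procedures done before chemotherapy and possibly the tests after it. It does not mention biopsy harm.
- Unplanned admissions are counted only during chemotherapy, and their definition includes no attribution to a cause.
- The application is the stated patient route for AEs, but the instruction to download it goes only to the intervention group. As written, this route misses controls and everyone before randomisation.

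**4. Size**

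Inputs: 790 participants, 1:1 randomisation and 10% drop-out (Estimated sample size and power); two test occasions (Population).
- Maximum sessions: 790 × 2 = 1,580.
- Before randomisation: up to 790, when nobody has an arm.
- After randomisation: up to 790, of which 790 / 2 = 395 are in the control arm.
- If 10% miss the pre-surgery test (an assumption that borrows the planned drop-out): 790 × 0.90 = 711 sessions after randomisation, about 711 / 2 ≈ 356 of them in controls, and 790 + 711 = 1,501 in total.

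These are counts of exposure, not of harm. The protocol gives no event rate for the tests or biopsies.

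**The case against.** The strongest reply is that the protocol deliberately restricts documentation to events of specific interest in a low-risk behavioural trial. On this view a site would naturally record a test injury as exercise-related, and serious consequences would surface in any case as recorded symptoms or unplanned admissions. The cycle test is submaximal and the leg test yields a hypothetical 1-RM, so few events are likely.

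Much of this stands. It defeats four stronger conclusions that a reader might draw:
- *Harm from testing can never be recorded, and the pre-randomisation part of the window must be empty.* The documents do not support this. The term exercise-related can be read to include the tests, and Ethical considerations promises wider recording during chemotherapy.
- *Half of the 1,580 sessions are control-arm sessions.* The baseline tests precede randomisation, so at most about 395 are.
- *Every participant has three extra cores and research blood samples.* The Study calendar marks these as Stockholm only. The single biopsy in all participants comes from a different section, and the two statements of scope need reconciling.
- *The window opens at consent in order to capture procedure-related harm.* The protocol gives no reason for the start date.

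What does not stand is that the gap is harmless. None of the text relied on gives biopsy or blood-sampling harm an AE or SAE route. The text that might cover testing contradicts the documentation rule. This is also not detail left to an analysis plan, since the protocol states the reporting rules explicitly.

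**Conclusion.** The point holds in a limited form. As written, Adverse Events gives no AE or SAE route for harm from study-specific biopsies or research blood sampling, in either arm, although recording opens at consent. For the strength and cycle tests there is no clear route. The exposure is up to 1,580 test sessions: up to 790 before randomisation and at most about 395 in controls afterwards. To these are added the biopsies and blood draws, in a group that the protocol defines inconsistently.

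This rests on three assumptions: that the trial intervention means the exercise programme, which the Study calendar contrasts with usual care; that the calendar's order is the order of events, with baseline items before randomisation; and, for the maximum counts, that all 790 participants attend both test occasions. The number of events missed cannot be estimated from the documents and may well be small. The point is worth correcting because it concerns safety oversight and costs little.

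**What to change.** 1. In Adverse Events, extend the AE filter, the causality scale and the SAE rule to cover *the trial intervention or a trial-mandated procedure (study-specific biopsies, research blood sampling, strength and cycle tests)*, in both arms and from consent.
2. Tabulate procedure-related events separately from exercise AEs, so that the exercise AE rate keeps its meaning.
3. Name recording by the investigator or site as the route for control-arm and pre-randomisation events. Rewording the definitions alone would leave these participants without a stated reporting channel.
4. Reconcile Adverse Events with Ethical considerations on which events are recorded and over what period. State how the sentence on leaving the trial after a serious adverse event applies to a procedure-related one. That decision belongs to the sponsor and investigators, but widening the SAE rule without addressing it could bring biopsy or test events under that sentence in both arms.
5. Reconcile the Study calendar with Tumour microenvironment on who is biopsied.

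The cost is a protocol amendment, one CRF category and a few extra event forms. No new procedure is needed. Sites take on the modest task of asking about and recording procedure-related events in participants who do not use the application.

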### Intervention

Participants randomized to the exercise group will complete two 60-min home-based exercise sessions per week from initiation of NACT to surgery (approx. five months) via a mobile application. To digitalise exercise interventions:

- Patients will receive instructions by an exercise physiologist or physiotherapist and perform training via the individualised training mobile application Vitala, supported by contact with a local physiotherapist/physiologist and remotely via zoom.
- The Vitala mobile phone application provides exercise instructions and support and measures program adherence and symptom reporting. Videos of variations of the resistance training and high-intensity interval training (HIIT) exercises are included in the app and are individually adapted to each participant.
- Initial exercise intensity will be individually tailored to each patient’s fitness at baseline and rate of perceived exertion during the program and adapted if required
- Sessions will begin with a 3-minute moderate intensity (12-13 on Borg’s Rate of Perceived Exertion (RPE) scale) warm-up.

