#### Handling missing values and deaths

Experience from previous studies have shown that this group of patients are in general highly motivated to fully participate in trials, including answering questionnaires, undergo physical exams and other assessments. Hence, it is anticipated that the dropout rate and the number of missing values will be low in both treatment arms and that this will be a minor problem in this study. Furthermore, the number of deaths during this relatively short follow-up period is also expected to be low. Nevertheless, sensitivity analysis will be performed where missing values will be assumed to be missing at random, MAR. This assumption will be already accommodated in the mixed models where repeated measurement outcomes will be analysed. For the remaining outcomes multiple imputations, assuming MAR will be performed.

A data monitoring committee consisting of three independent experts will perform a safety analysis with the purpose to assess the recruitment to the trial and the rate of adverse events, and to make sure that patients in the intervention group do not appear to fare significantly worse than patients in the standard of care group. The committee may recommend terminating the study if a significant benefit in favour of one group is shown, such that the HR for intervention versus standard of care significantly (p=0.001) exceeds 1, if the recruitment is so low that that the necessary number of events is unlikely to be reached or if there are serious concerns about unexpected AEs in the intervention group. If the committee determines that it is safe to proceed with the study, the results of the analysis will remain unknown to everyone except the committee members.

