## Ethical considerations

The original version of this trial protocol has been approved by the Ethics Committee of the Karolinska Institutet, Stockholm (Dnr 2022-02084-01).

Physical exercise during chemotherapy is deemed feasible and safe^19^. Potential adverse events, such as cardiovascular and musculoskeletal symptoms, will be recorded throughout the NACT period and participants who experience serious adverse events will discontinue trial participation. Adverse events that are ascribed NACT but not the trial intervention will be handled in accordance to clinical routine by the responsible oncologists. There is no evidence that the intervention may lead to inferior results concerning the primary or secondary endpoints. Instead, there are data from studies in the adjuvant setting showing a preserved health-related quality of life, lower rate of self-reported symptoms related to treatment, and higher chemotherapy completion rates. In addition, this trial offers patient empowerment that is generally experienced as a positive aspect of treatment. Therefore, participation in this trial is judged ethically highly feasible.

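### The severe-pain example in the adverse-event rule is narrower than the list it illustrates, so sites could record exercise pain differently (minor)

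*Protocol*

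**What the plan says.** All of the recording rule stands in the protocol section Adverse Events. It first limits the scope: "The local investigator will only document AEs of specific interest in relation to the intervention, which are exercise-related AEs". Three list items then define these events:

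- Item 1: "requiring treatment or talking to a doctor or other health professional".
- Item 2: a persistent worsening of health or well-being and, after a comma, "new occurrence of substantial pain or swelling e.g. muscle tear".
- Item 3: an event during or after a session "requiring restrictions/alterations or early termination of the exercise, or any treatment or clarification by a physician".

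Three examples follow. The one on pain reads: "patient-experienced severe pain after exercise is reported as an AE if it requires contact with a treating physician". A muscle tear during a session is an adverse event without further condition. Dizziness or nausea counts when it leads to the session being stopped early. The section also states one exclusion: programme changes made because of recent oncological treatment or metastases are not adverse events.

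Three other places matter. Under Intervention, participants train at home through the app, "supported by contact with a local physiotherapist/physiologist and remotely via zoom". Under Ethical considerations: "Potential adverse events, such as cardiovascular and musculoskeletal symptoms, will be recorded throughout the NACT period". Under Handling missing values and deaths, the data monitoring committee's safety analysis is "to assess the recruitment to the trial and the rate of adverse events", among other purposes.

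**The concern.** Pain after exercise is among the most foreseeable harms of this intervention, and the example on pain is the line that site staff are likely to apply when a participant reports it. Its trigger, contact with a treating physician, is narrower than item 1 of the list and, on one reading, narrower than item 2. The protocol does not say which governs when the two differ.

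The gap falls on the trial's normal route of contact. A participant training at home who has pain after a session will often turn first to the physiotherapist or physiologist who supports the programme. Item 1 covers that contact and the example does not mention it.

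At stake is how consistent the exercise-safety record is between sites. The Time plan foresees 10 Swedish and 1 to 7 Finnish sites, and Monitoring and follow-up assigns monitoring outside Sweden to other CROs. Uneven application of one paragraph would make the recorded rate depend partly on the site. Because the example is the narrower of the two, the error could go only towards fewer recorded events.

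**Working it through.** The protocol states no figure on this point and none can be recomputed. The check is to put one case through each part of the text.

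**Test case.** A participant has new, severe pain after a session. The trial physiotherapist or physiologist deals with it, and no physician is contacted.

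| Part of the rule | Condition | Is the case recorded? |
| --- | --- | --- |
| Item 1 | Treatment, or talking to a doctor or another health professional | Yes: the physiotherapist is a health professional |
| Item 2 | Persistent worsening; new substantial pain or swelling | Arguably yes. The comma leaves it unclear whether new pain is enough in itself or must also be a persistent worsening |
| Item 3 | Exercise restricted, altered or stopped early; or treatment or clarification by a physician | Yes if the exercise was changed or stopped |
| Pain example, read as an illustration | Contact with a treating physician is one case that counts | Not addressed; the list decides, so yes |
| Pain example, read as a threshold | Contact with a treating physician is needed | No |

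**Step 1: what the list gives.** Item 1 settles the case without help from item 2 or item 3. The doubt about item 2's comma therefore does not change the result.

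**Step 2: what the example gives.** It says that severe pain is reported *if* a physician has to be contacted, in a sentence offered as some examples. As logic this is one sufficient case and excludes nothing.

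**Step 3: why a site may still read it as a threshold.** If severe pain handled by any health professional is recordable anyway, the words about a treating physician do no work. They have a purpose only as a limit. The dizziness example is built the same way, with a condition (early termination) that matches item 3. A reader who takes that condition as the test for dizziness will naturally take the physician condition as the test for pain. The muscle-tear example proves little either way, because item 2 names muscle tear outright.

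**Step 4: does another route close the gap?** Patients are told to report adverse events in the app, which needs no physician. But the local investigator assesses and records the events and judges causality and severity. An app entry assessed against the narrower example could stay out of that record.

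**Result.** The same event is recorded under the list and could be left out under the example read as a threshold.

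**Size.** The number of events affected is the number of severe-pain episodes, times the share handled without a physician, times the share of sites (weighted by participants) that let the example govern. The documents give none of the three, so no estimate is offered.

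**The case against.** The strongest case on the other side is that there is no conflict. The list is the definition and the examples illustrate it. The pain example says *if*, and an example does not restrict a rule. Where the section wants to exclude something it says so, as it does for programme changes due to oncological treatment. The test case is covered by item 1, the app gives patients a second way to report, and Ethical considerations says that musculoskeletal symptoms will be recorded during neoadjuvant chemotherapy. All of this favours the broad reading.

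Most of this stands. It rules out two stronger conclusions that a reader might infer:

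- *That the protocol contradicts itself and records severe pain only after contact with a physician.* The text does not say *only if*. The event goes unrecorded only where a site lets the example override the list.
- *That the reported safety of the exercise programme will be too favourable.* This would need sites to follow the example in practice and a material number of episodes to be handled without a physician. The documents establish neither.

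The consequence for the committee is also limited. Its ground for stopping that concerns adverse events is serious concern about unexpected events, whereas musculoskeletal symptoms are expected. Reporting of serious adverse events rests on seriousness and relatedness, and the example does not affect it.

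What the objection does not remove is the practical point. Examples are there to show staff how to apply the rule, and this one names a narrower contact than the rule does, in a trial where the usual contact is not a physician.

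**Conclusion.** The point holds as a minor one. The severe-pain example is narrower than the defining list, and the protocol does not say that the list prevails. Recording of exercise pain handled by the physiotherapist could therefore differ between sites, and the exercise adverse-event rate that the committee sees could be understated. The direction is clear, because the example can only remove events; the amount cannot be estimated from the documents.

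The conclusion rests on two assumptions: that at least some sites would use the example as their working test, and that some severe pain is settled without a physician. The second is plausible given how the programme is supported. Neither can be verified from the protocol. The primary endpoint, the sample size and the efficacy analyses are untouched.

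**What to change.** In Adverse Events, reconcile the pain example with the list. One way is to replace the condition about a treating physician with *if it meets any of the criteria above*. Also state before the list that meeting any one item is enough. That sentence makes clear that the three items are alternatives and that the list governs the examples. The list items can stay as they are, and the change concerns only what is recorded.

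The cost is a short text change, a note in site training, a few more adverse-event forms, and a reported adverse-event rate that may be slightly higher.
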